Our data of over half of the Brazilian population will help understand both (observationally) the association of multiple factors on both mental illness and suicide, and the impact of interventions targeting some of these factors. Within each broad analysis, we will explore pathways, mechanisms and interactions/moderators. This is especially important in LMICs, such as Brazil, where implementing preventative measures may be more challenging as a result of cultural and socioeconomic factors, limited resources, as also in large continental countries because of size and distribution of the population [15]. This study’s aims are as follows:
To use large national datasets to evaluate the effect of a broad range of social drivers and of a social-economic intervention on youth mental health,To test four mechanisms and pathways (reducing parental mental illness; increasing school retention; reducing exposure to violence; decreasing impulsivity) of the social-economic intervention on reducing mental illness among youth,To evaluate whether equity is a moderator of the effectiveness of the cash transfer program, e.g., whether the Brazilian cash transfer program improves the lives of the most vulnerable subgroups (with lower income, black population, and women) compared to less vulnerable groups, thereby reducing mental health disparities, andInvestigate early life exposures, intergenerational aspects, and to forecast the impact of socioeconomic changes and cash transfers mitigation effects in Brazil until 2030 using microsimulation models, also modelling the impact of the current COVID-19 related economic recession.

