#### Data and measures

Datasets, variables, and sample sizes.

***100 Million Brazilian Cohort*.** We will analyze a cohort of subjects registered in Unified Registry for Social Programs (CadÚnico). The CadÚnico is a data collection and storage system that contains individual records with demographic and socioeconomic information on the poorer half of the Brazilian population (n = 114,007,705). Anyone who meets the eligibility criteria can be registered by visiting one of the Centers for Social Assistance (CRAS) or be registered at home, as social workers visit households periodically to identify and register eligible individuals. The criteria to be eligible for CadÚnico registration are: having a monthly family income per capita of half the minimum salary in Brazil (778 reals in 2015) or less; or having a total family income (monthly) of up to three minimum salaries. The CadÚnico contains information about housing conditions, income and demographic characteristics of all the members of a registered family [26].

***Bolsa Familia Program (BFP)*.** The Brazilian Cash Transfer Program (BFP) is the largest poverty alleviation program in the world, with about 46 million people having received the benefit up to 2015. It has three aims: income supplement guarantee for immediate relief of extreme poverty (people who live with up to 70 reals per capita) [27]; access to public services (improving education, health, and citizenship of families); and productive inclusion to increase the capacity and job opportunities, and income generation among the poorest families [28].

In 2014, the eligibility criteria for participation in the program (which is more stringent than the conditions for eligibility to register in CadÚnico) was having an income of less than 77 reals (14 USD) monthly per person or less than 154 reals in cases where there is a child, adolescent or pregnant woman in the family. The benefits were: “basic benefit”, 77 reals monthly, regardless of family composition; an extra 35 reals to families with a child or adolescent between 0–15 years, or a pregnant or nursing woman; and an extra 42 reals per adolescent from 16–17 years, in 2014. Families living in extreme poverty can accumulate all these “basic benefits” to a maximum of 1,332 reals per month (235 USD).

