To evaluate the impact of the countrywide cash transfer program on those outcomes, we will run Regression Discontinuity Design (RDD), Propensity Score Matching (PSM), and difference-in-differences, which are robust methods of impact evaluation in public health. This should help to identify the best statistical techniques to evaluate the impact of BFP on mental health-related hospitalization and suicide. Different evaluation methods make different assumptions. For instance, PSM assumes that after matching for the observed characteristics, there is no unmeasured confounding for the association between the intervention and the outcome. RDD instead assumes that people just below and just above the threshold of a continuous variable used as eligibility criteria for the intervention are “similar” in all relevant respects. Therefore, the difference in the outcome between the intervention groups is practically random near the threshold. PSM is a method that has been used in large electronic health records [10, 32]. It allows for matching where a true case-control design was not possible, which is usually the case for electronic health records of the type we will use in this project. A propensity score is a scalar summary of measured characteristics prior to treatment (potential confounders). Therefore, treated, and untreated subjects with equivalent propensity scores, also present similar pre-treatment characteristics. This method permits the generation of a grouping between intervention and no intervention that mimics the state of randomization. In our study, people who were part of one of the aforementioned programs would have specific characteristics, to control for that we will find a match for them on the remaining dataset (114 million) considering their age, sex, educational level, income, location of residence (urban/rural), household living conditions including household density, water supply, sewage and garbage collection, previous psychiatric hospitalization, residency type and building material. This allows us to inspect whether these subjects are at a higher or lesser risk of developing mental illness later in their lives. We assume that if the PSM models’ findings are similar to RDD, the results are robust given the underlying assumptions of each different model.

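### Similar PSM and RDD results are taken to show robustness, although the two designs estimate effects in different populations; they should be compared among families near the cut-off

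*Protocol article*

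**What the plan says.** The protocol article (Analytic strategy, Aim 1) lists three designs for the effect of the programme: "we will run Regression Discontinuity Design (RDD), Propensity Score Matching (PSM), and difference-in-differences". It explains that they rest on different assumptions. It then assumes that if the PSM "findings are similar to RDD, the results are robust given the underlying assumptions of each different model". Difference-in-differences plays no part in that sentence.

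The same paragraph describes whom each design compares. RDD concerns "people just below and just above the threshold of a continuous variable used as eligibility criteria for the intervention". PSM starts from programme participants in general: "we will find a match for them on the remaining dataset (114 million" people), using age, sex, education, income, residence, housing conditions and previous psychiatric hospitalization.

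Under Data and measures, the 2014 eligibility rule is an income of "less than 77 reals (14 USD) monthly per person or less than 154 reals in cases where there is a child", an adolescent or a pregnant woman in the family.

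Aim 3 (Background) asks whether the programme "improves the lives of the most vulnerable subgroups (with lower income, black population, and women) compared to less vulnerable groups".

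**The concern.** Comparing two designs tests their assumptions only if both estimate the same quantity. Here one is local to the cut-off and the other averages over matched beneficiaries across the income range. A difference between them may reflect effect variation rather than bias. A match may reflect bias that happens to close a real gap. The sentence reads a match as robustness without asking for which population.

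The stake reaches beyond Aim 1. RDD and PSM are used again for Aims 2 and 3. In Aim 4, the effect estimates from the retrospective analyses feed projections to 2030, including a scenario that extends coverage to the newly poor. Whether an effect belongs to families near the cut-off or to all beneficiaries matters for such projections.

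**Working it through.** **Step 1. Target of each design, as described.**

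| Design | Compared | Effect estimated |
|---|---|---|
| RDD | People just either side of an eligibility threshold | Effect near the cut-off |
| PSM | Participants matched to others in the cohort | Average over beneficiaries who find a match |

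The cohort holds 66,079,181 beneficiaries and 47,928,524 non-beneficiaries. The sum is 114,007,705, the total given under Data and measures. Nothing in the article confines PSM to families near a cut-off.

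**Step 2. When the two coincide.** Let R_c be the rate ratio near the cut-off, R_d that in a poorer band of beneficiaries, and s the share of beneficiaries in the poorer band. With equal baseline risk in both bands:

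- unbiased RDD gives R_c;
- unbiased PSM gives s × R_d + (1 − s) × R_c.

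These are equal when R_d = R_c. If R_d differs from R_c, they differ for any s above 0.

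**Step 3. Illustration.** The article gives no rate ratios and no value of s, so every input here is assumed: R_c = 0.95, R_d = 0.80 or 0.70, s = 50–90%. The last two columns give R_c divided by the unbiased PSM value. This is the upward confounding factor in PSM that would make it equal RDD exactly.

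| s | PSM, R_d = 0.80 | PSM, R_d = 0.70 | RDD | Factor, 0.80 | Factor, 0.70 |
|---|---|---|---|---|---|
| 50% | 0.875 | 0.825 | 0.95 | 1.09 | 1.15 |
| 60% | 0.860 | 0.800 | 0.95 | 1.10 | 1.19 |
| 70% | 0.845 | 0.775 | 0.95 | 1.12 | 1.23 |
| 80% | 0.830 | 0.750 | 0.95 | 1.14 | 1.27 |
| 90% | 0.815 | 0.725 | 0.95 | 1.17 | 1.31 |

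Example at s = 60%: 0.6 × 0.80 + 0.4 × 0.95 = 0.86, and 0.95 / 0.86 = 1.10. With R_d = 0.95 every PSM entry is 0.95 and every factor is 1.00.

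**Step 4. What near the cut-off means here.** For 2014 the article gives 77 reals, or 154 reals where there is a child, adolescent or pregnant woman. Two families with the same income, say 100 reals per person, can lie on opposite sides of their own cut-offs. A common population near the cut-off therefore has to be defined by the distance of income from the cut-off that applies to that family in that year.

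**The case against.** The sentence is modest. It is worded as an assumption, it is conditional on each model's own assumptions, and agreement between designs that can fail in different ways is a recognised form of support. If the effect is constant over income, the two should agree. Matching on income may also drop beneficiaries with no comparable non-recipient, which could pull PSM towards the cut-off. The plan repeats its analyses by income level and adds difference-in-differences.

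Much of this stands. Agreement has some value, and the gap may be small. But conditioning on the models' assumptions does not help, because both sets can hold while the estimates differ. Stratifying by income does not by itself put the two designs on a common population. How far matching would shift the PSM population is not stated.

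A reader might infer more than the article supports:

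- **That agreement proves validity, or that disagreement means not robust.** The text assumes the first and says nothing on the second.
- **That Aim 3 predicts a difference.** It asks whether effects differ; the conceptual framework uses conditional language.
- **That the RDD is fixed at one wrong threshold.** The passage defines RDD in general terms and sets no cut-off. Bandwidth, handling of imperfect take-up and diagnostics may sit in a fuller plan.
- **That only families in extreme poverty accumulate benefits, so the dose must differ.** The article says they can accumulate all benefits; the restriction is not stated. The 70-real figure is undated and need not contradict the 2014 figure of 77.
- **That non-recipients at the same income show confounded receipt.** Cut-offs differ by family composition, so such families can exist even if receipt follows eligibility exactly.
- **That the design will be picked by its result.** The article says of the several designs: "This should help to identify the best statistical techniques to evaluate the impact of BFP". What follows discusses assumptions, not estimates.

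**Conclusion.** The robustness sentence claims more than the comparison can carry. As described, RDD and PSM have different target populations. If the effect varies with income, agreement is neither necessary nor sufficient for validity, and confounding in PSM could produce it. Agreement is then weak supporting evidence, and it does not carry over to all beneficiaries.

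This conclusion needs only the article's own descriptions of the designs and the possibility, left open by Aim 3, that the effect varies with income. The size is not known. A gap of 0.83–0.86 against 0.95, and confounding of 10–14% to hide it, are illustrations under assumed rate ratios, assumed shares of 60–80% and equal baseline risk. With a constant effect the gap is zero.

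**What to change.** 1. State the target population of each design.
2. Define the RDD running variable as per-capita income minus the cut-off that applies to the family type and year.
3. Refit PSM only among families inside the RDD bandwidth, and compare the two designs in that common population. Report how many beneficiaries there find a match: where receipt follows eligibility closely, overlap may be thin.
4. Replace the robustness sentence with wording such as: Agreement between PSM and RDD among families near the cut-off will be read as supporting evidence for the effect in those families only, and not for the effect in all beneficiaries.

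The cost is a change of wording and one restricted PSM run, whose interval will be wider than that of the full matched analysis. The full PSM analysis can stay as an estimate for matched beneficiaries, resting on its own assumption of no unmeasured confounding.

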**Aim 2: To test four mechanisms and pathways of the social-economic intervention on reducing mental illness among youth; and Aim 3: To evaluate whether equity was a moderator of the effectiveness of the cash transfer program**, **e.g., whether the Brazilian cash transfer program improved the lives of most vulnerable subgroups (with lower income, black population, and women) compared to less vulnerable groups reducing mental health disparities.**

We will evaluate whether BFP program affects youth mental health through improving social drivers by running Regression Discontinuity Design (RDD) and Propensity Score Matching (PSM), and Structural Equation Modelling (SEM) for each of them and the outcomes. Such strategies allow us to examine the pathways by testing the impact of the intervention on variables that might be on the pathway of the relation between BFP and mental health outcomes. We hypothesize that BFP has an effect on reducing mental health-related hospitalizations and suicide among youth because it also affects their social drivers. Stratified analyses by municipality size, regions, states, and levels of Human Development Index (HDI) will also be performed.

We will include a set of covariates recognized as social drivers of mental illness for youth at the individual level such as income, income instability, unemployment, isolation and at the contextual level, variables from the municipalities where the youth live, such as population, fertility, mortality, migration, housing characteristics, characteristics of the neighbourhood, municipal income, labour, economic inequality (Gini index), Human Development Index (HDI), proportion of poor people and municipal coverage of the community mental health center and number of mental health professionals in the same municipality. We will also evaluate whether equity was a moderator of the effectiveness of the cash transfer program, e.g., whether the Brazilian cash transfer program improved the lives of most vulnerable subgroups compared to less vulnerable groups, thereby reducing mental health disparities. Therefore, we will repeat the analysis stratifying by subgroups with diverse ranges of income level, black compared with the white population, and female compared to male.

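### Aim 3 repeats the regression discontinuity analysis within income ranges, although income is the variable that defines the discontinuity, so that method cannot inform moderation by income

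*Protocol article*

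**What the plan says.** - **Question.** Under Analytic strategy, the heading for Aims 2 and 3 gives the third aim as "To evaluate whether equity was a moderator of the effectiveness of the cash transfer program". It names lower income, black population and women as the vulnerable groups.
- **Method for the pathways and outcomes.** The same text proceeds "by running Regression Discontinuity Design (RDD) and Propensity Score Matching (PSM), and Structural Equation Modelling (SEM) for each of them and the outcomes".
- **Method for moderation.** The plan then says "we will repeat the analysis stratifying by subgroups with diverse ranges of income level, black compared with the white population", and adds the two sexes as a third comparison. It gives no income bands, between-stratum contrast or effect scale, and it does not except any of the methods.
- **What RDD relies on.** Under Aim 1, RDD is described as a comparison of "people just below and just above the threshold of a continuous variable used as eligibility criteria for the intervention".
- **What decides eligibility.** Data and measures gives the 2014 rule as "having an income of less than 77 reals (14 USD) monthly per person or less than 154 reals", the higher figure applying where the family includes a child, an adolescent or a pregnant woman.
- **Robustness rule.** Under Aim 1, agreement between PSM and RDD findings is to be taken as evidence that results are robust.
- **Related statements.** The aims at the end of the Background promise to explore interactions and moderators in every broad analysis. The Conceptual framework promises an evaluation of differential impact by race and gender.

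**The concern.** Stratifying an RDD by its own running variable removes the contrast the design depends on. The article does not name the running variable. However, per-person income is the only continuous eligibility criterion it gives for BFP, so the inference is secure.

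Lower income is the first vulnerable group that Aim 3 lists. If RDD is run in income bands as written, some bands will yield nothing interpretable and others will repeat the overall result. Differences between those outputs could be mistaken for moderation by income. The protocol's safeguard of comparing PSM with RDD would also be missing for this moderator.

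A smaller point concerns race and sex. Moderation is a statement about the difference between two effects, and the operative sentence names only the separate analyses.

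**Working it through.** The article gives no sample size, power, significance level or effect size for Aim 3, so there is no design figure to reproduce. The main check is a matter of identification. The numbers in steps 2, 5 and 6 illustrate it; apart from the cut-offs of 77 and 154 reals, they are assumed.

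**Step 1: what RDD estimates.** Let X be income per person, c the cut-off, and Y the outcome. RDD estimates

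τ(c) = lim E[Y | X = x] as x rises to c − lim E[Y | X = x] as x falls to c,

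divided by the jump in BFP receipt at c if take-up is incomplete. Both limits are needed. Within an income band from a to b, τ(c) exists only if a < c < b. If it exists, it does not depend on a or b. The band adds nothing except possible loss of data near the cut-off.

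**Step 2: illustrative bands.** The cut-offs of 77 and 154 reals come from Data and measures (2014). The bands are assumed, because the article states none.

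| Assumed bands (reals per person) | 77 inside a band? | 154 inside a band? |
|---|---|---|
| 0–38.5, 38.5–77, 77–154, 154+ | no (band edge) | no (band edge) |
| 0–70, 70–140, 140+ | only in 70–140 | only in 140+ |

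With the first set, no band supports an RDD. With the second, the poorest band supports none, and the other two return τ(77) and τ(154).

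**Step 3: can the two cut-offs stand in for an income comparison?** τ(77) and τ(154) are distinct local effects at different incomes. Under the stated rule, though, the higher limit applies to families with a child, an adolescent or a pregnant woman. The difference between the two effects therefore mixes income level with household composition. It also says nothing about youth well below 77.

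**Step 4: the robustness rule.** PSM within an income band estimates an effect over the matched people in that band. RDD estimates nothing there, or an effect at one point. No RDD counterpart exists against which to check PSM for income moderation.

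**Step 5: race and sex.** These variables do not assign BFP, so each stratum can contain people on both sides of the cut-off and RDD remains possible. The moderation estimate follows from the stratum estimates:

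d = b₁ − b₂, SE(d) = √(s₁² + s₂²).

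Assume risk ratios of 0.85 and 0.92 with SE(log RR) 0.05 each:
- Separate strata: p = 0.001 and p = 0.095.
- Contrast: ratio of risk ratios = 0.85/0.92 = 0.92; SE = √(0.05² + 0.05²) = 0.071; 95% CI 0.80 to 1.06; p = 0.26.

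With assumed risk ratios of 0.80 and 0.95 and the same SEs, the ratio is 0.84 (95% CI 0.73 to 0.97; p = 0.015). The explicit contrast answers the question and can be formed from the planned strata.

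**Step 6: scale.** Assume rates of 20 and 10 in two groups and the same risk ratio of 0.85 in both. The rates become 17.0 and 8.5, reductions of 3.0 and 1.5. The gap falls from 10 to 8.5 with no moderation on the ratio scale. Because Aim 3 concerns reducing disparities, the absolute scale needs to be reported.

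**The case against.** The strongest reply is that only the RDD part is at issue. PSM, SEM and difference-in-differences need no cut-off inside an income band. Income is already a PSM matching variable, and the unspecified ranges could be chosen within the eligible population, so moderation by income can still be studied. This stands, and it limits the point to RDD and to the check that depends on it.

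The reply continues that a condensed article may leave the form of the contrast and its scale to a fuller document. The Background and Conceptual framework do announce interactions, moderators and differential impact. This largely stands as well. For race and sex the recommendation is therefore a clarification.

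Three stronger readings are tempting, and the documents do not support them:

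- **That Aim 3 cannot show moderation by race or sex.** Stratum estimates can be contrasted directly, and the article announces that differential impact will be evaluated.
- **That moderation will be judged by significance in one stratum and not in the other.** No section adopts that rule or states power per stratum. A chance of discordant significance is therefore not a measure of this plan's error.
- **That higher-income strata contain no treated people.** The limits quoted are for 2014, while the data run from 2001 to 2018. Registration is also open through total family income, so income per person is not capped at the per-person criterion. Table 1 counts 66,079,181 beneficiaries among 114,007,705 people (58%) but gives no split by income. Comparing the registration and eligibility ceilings would give a share of an income axis, not of people.

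What the reply does not remove is that the text names RDD, repeats the analysis by income and makes no exception.

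**Conclusion.** The point holds in limited form. As written, Aim 3 includes an income-stratified RDD that is either not identified or only local to a cut-off. It cannot compare poorer with less poor youth, and it leaves moderation by income without the PSM-versus-RDD check.

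The extent is one method for one of three moderators (income, race, sex). No numerical magnitude can be derived, because the article gives neither income bands nor counts by income. The conclusion rests on two readings: that per-person income is the RDD running variable, and that the repeated analysis includes RDD. It does not depend on the 2014 cut-offs. If the cut-offs moved over the study years, a given band might contain one in some years, but the effect would still be local to it.

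The conclusion does not extend to a claim that Aim 3 fails for race or sex, or that moderation by income cannot be estimated by any planned method.

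**What to change.** In the Aims 2 and 3 text under Analytic strategy:

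1. Exclude RDD from the income stratification, and report RDD effects only as local to each eligibility cut-off.
2. Estimate income moderation by PSM, weighting or difference-in-differences with a BFP-by-income interaction. Restrict it to the income range where beneficiaries and non-beneficiaries overlap, and present that overlap, for example as counts of each by income band.
3. State that the PSM-versus-RDD comparison does not apply to income moderation.
4. For race and sex, keep the strata, but base the moderation conclusion on the between-stratum difference (the interaction) with its 95% CI. Include the absolute scale alongside any ratio.

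This needs changed wording and one contrast per moderator, with no new data. The drawback is that the income conclusion will apply only to the overlap range and will rest on methods that assume no unmeasured confounding (PSM or weighting) or parallel trends (difference-in-differences), without RDD support.
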